# Examining the benefit of graduated compression stockings in the prevention of hospital-associated venous thromboembolism in low-risk surgical patients: a multicentre cluster randomised controlled trial (PETS trial)

**DOI:** 10.1136/bmjopen-2022-069802

**Published:** 2023-01-17

**Keywords:** thromboembolism, surgery, vascular medicine

## Abstract

**Introduction:**

Hospital-acquired thrombosis (HAT) is defined as any venous thromboembolism (VTE)-related event during a hospital admission or occurring up to 90 days post discharge, and is associated with significant morbidity, mortality and healthcare-associated costs. Although surgery is an established risk factor for VTE, operations with a short hospital stay (<48 hours) and that permit early ambulation are associated with a low risk of VTE. Many patients undergoing short-stay surgical procedures and who are at low risk of VTE are treated with graduated compression stockings (GCS). However, evidence for the use of GCS in VTE prevention for this cohort is poor.

**Methods and analysis:**

A multicentre, cluster randomised controlled trial which aims to determine whether GCS are superior in comparison to no GCS in the prevention of VTE for surgical patients undergoing short-stay procedures assessed to be at low risk of VTE. A total of 50 sites (21 472 participants) will be randomised to either intervention (GCS) or control (no GCS). Adult participants (18–59 years) who undergo short-stay surgical procedures and are assessed as low risk of VTE will be included in the study. Participants will provide consent to be contacted for follow-up at 7-days and 90-days postsurgical procedure. The primary outcome is the rate of symptomatic VTE, that is, deep vein thrombosis or pulmonary embolism during admission or within 90 days. Secondary outcomes include healthcare costs and changes in quality of life. The main analysis will be according to the intention-to-treat principle and will compare the rates of VTE at 90 days, measured at an individual level, using hierarchical (multilevel) logistic regression.

**Ethics and dissemination:**

Ethical approval was granted by the Camden and Kings Cross Research Ethics Committee (22/LO/0390). Findings will be published in a peer-reviewed journal and presented at national and international conferences.

**Trial registration number:**

ISRCTN13908683.

Strengths and limitations of this studyThis is the first randomised controlled trial evaluating the role of graduated compression stockings (GCS) in the prevention of hospital-associated venous thromboembolism (VTE) in short-stay surgical patients who are assessed as low risk of developing hospital-associated VTE.The primary outcome is clinically meaningful and objective in nature.The cost-effectiveness analysis will assess the economic implications of providing GCS for the prevention of VTE in low risk, short-stay surgical patients.Given this is a cluster design, it will be important to demonstrate that the populations are balanced in terms of confounding factors that is, that the clustering has been successful.

## Introduction

Hospital-associated thrombosis (HAT) is defined as any venous thromboembolism (VTE)-related event during a hospital admission or occurring up to 90 days post discharge 1, and is a term that encompasses both deep vein thrombosis (DVT) and pulmonary embolism (PE). HAT accounts for significant morbidity and mortality with 57.1 VTE-related deaths per 100 000 hospital admissions reported in the year 2018–2019 within the UK National Health Service (NHS).^1^ The probability of untreated moderate-risk surgical inpatients developing HAT was previously estimated to be as high as 15%, this reducing to 4.1% with pharmacological and mechanical prophylaxis.^2^

Previously, UK annual VTE-related mortality was estimated to be 32 000 fatalities if thromboprophylaxis was not used, with associated costs of £640 million per annum.^3^ Surgery is an established risk factor for VTE.^4^ It is estimated that the risk of VTE for patients undergoing most general surgical, urological or open gynaecological procedures without thromboprophylaxis is 10%–40%.^5^ Furthermore, for those undergoing hip or knee arthroplasty, this risk increases to 40%–80%.^5^ Specific surgical factors such as abdominal and pelvic procedures, operations for cancer and procedures with a greater duration are associated with a greater risk of VTE.^6 7^ Conversely, operations with short anaesthetic and procedure times, that can be performed within a <48 hour hospital stay, and that permit early ambulation are associated with a low risk of VTE.^8^

Mechanical thromboprophylaxis in the form of graduated compression stockings (GCS), also known by a brand name ThromboEmbolic Deterrent,^5 9 10^ is often used. GCS apply a level of graduated pressure at rest, that is, not while ambulant; they are designed for immobile patients at risk of VTE. However, it has recently been shown that GCS provide no added benefit in the reduction of HAT for moderate and high VTE risk surgical inpatients receiving prophylactic dose of low-molecular-weight heparin (LMWH).^11^ Additionally, the CLOTS 1 trial, which randomised patients with acute stroke to either standard care alone or the combination of GCS and standard care, reported no difference in the rate of DVT.^12^ The findings of these and other studies have cast doubt on the use of GCS in prevention of VTE. Importantly, the patients in the aforementioned trials were at a higher risk from the distinct low VTE risk group.

Limited evidence is available on the rate of HAT in low-risk surgical patients. In the UK, National Institute for Health and Care Excellence (NICE) guidelines for the prevention of VTE published in 2007 previously recommended that all surgical patients should receive GCS to reduce the risk of VTE, irrespective of the absence of thrombosis risk factors.^13^ The subsequent updated NICE guidelines did not include this blanket recommendation, but instead provided specific recommendations for differing procedure types. The most contemporary NICE guidelines, published in 2018, recommend that all patients undergoing abdominal, thoracic, spinal, bariatric, head and neck and elective joint surgery should be treated with GCS, and to consider treatment with GCS for all those undergoing cardiac, vascular and ear, nose and throat surgery.^14^ The interpretation of these recommendations has meant that patients undergoing short-stay procedures, who are able to ambulate early and have no other thrombosis risk factors are still treated with GCS. Hence, it is now common practice for patients undergoing day case procedures, even those that have no other assessed risk factors, to be prescribed GCS in the absence of contraindications.

The evidence to support GCS for short-stay ambulant patients is poor. A systematic review^15^ examining the use of GCS in comparison to no prophylaxis in low VTE risk short-stay surgical patients confirmed that there have been no randomised controlled trials (RCTs) to support this practice. Furthermore, a meta-analysis in the 2018 Cochrane Review for patients at moderate and high-risk of VTE revealed a significantly lower OR of DVT in those treated with GCS in comparison to those that were not.^16^ However, none of the included 18 surgical RCTs identified in the review consisted of low-risk procedures, that is, ambulatory day case procedures.

Moreover, the UK National Institute for Health Research Health Technology Assessment-funded GAPS trial, assessing the use of GCS in addition to LMWH for the prevention of VTE in moderate and high-risk (ie, not low risk) elective surgical patients, demonstrating that LMWH alone was non-inferior to dual thromboprophylaxis with LMWH and GCS, has further drawn the role of GCS in the prevention of VTE in surgery into question.^11^ This is on the background of other RCTs, such as the CLOTS 1 trial which randomised patients with acute stroke to either standard care or the combination of GCS and standard care and reported no difference in the rate of DVT.^12^ While the clinical community are adopting the GAPS trial findings into clinical practice, they cannot safely be extrapolated to this large cohort of low VTE risk patients who do not also receive LMWH.

Hence, due to this paucity of evidence to support the use of GCS in the prevention of VTE for low VTE risk surgical patients, an adequately powered trial is required to provide evidence in relation to this practice.

### Objectives

The primary objective is to evaluate the potential benefit of GCS in the prevention of HAT in patients undergoing short-stay surgical procedures, assessed as being at low risk for VTE. Secondary objectives include comparisons of quality of life (QoL) at 7-days and 90-days, mortality at 90-days and a cost-effectiveness analysis.

## Methods and analysis

### Trial design

This is a prospective, multicentre, cluster RCT with a follow-up of 3 months. The primary outcome is assessed blindly.

### Study setting

Eligible participants will be recruited from at least 50 NHS Trusts/Health Boards sites in the UK. A complete list of actively recruiting study sites can be obtained from https://clinicaltrials.gov/ct2/show/NCT05347550.

### Eligibility criteria

Inclusion criteria are adult patients aged 18–59 years of age (as age 60 scores 1 point on risk assessment) scheduled to undergo a surgical procedure with a hospital stay <48 hours who are assessed as being at low risk of developing VTE as per the Department of Health risk assessment tool (ie, no assessed thrombosis risk factors/scoring 0).^17^ Exclusion criteria include individuals with a contraindication to GCS; assessed as being at moderate or high-risk of VTE as per the Department of Health risk assessment tool; requiring therapeutic anticoagulation; with thrombophilia or thrombotic disorders; with a previous history of VTE; requiring intermittent pneumatic compression therapy beyond theatre and recovery; requiring extended thromboprophylaxis beyond discharge; female of childbearing age who have a positive pregnancy test; those with lower limb immobilisation; those unable to provide informed consent.

### Interventions

Centres randomised to the intervention arm, which is the current standard of care, will consist of participants receiving GCS. Clinical staff (eg, theatre support workers) will issue stockings to all patients who are scheduled to undergo short-stay surgery. Participants will be instructed to wear their stockings just before undergoing the surgical procedure and to remove the stockings as soon as they are ambulant after the procedure.

In those centres randomised to the control arm, participants will not receive GCS.

Figure 1 is a diagram displaying the participant flow in the trial.

**Figure 1 F1:**
[figure not shown]
PETS study flow chart. DVT, deep vein thrombosis; EQ-5D, EuroQol-5 Dimension; GCS, graduated compression stockings; HAT, hospital-acquired thrombosis; PE, pulmonary embolism; VTE, venous thromboembolism.

### Primary outcome

The primary outcome is the rate of symptomatic VTE during admission and/or within 90 days after discharge for surgical patients undergoing short-stay procedures assessed as being at low risk of VTE, in those treated with or without GCS.

### Secondary outcomes

The secondary outcomes include:

Mortality rates in each group.Adverse events (AEs) related to the GCS (assessed at 7 days, in those enrolled in the intervention clusters only).QoL score at 7-days and 90-days postsurgical procedure assessed using the EuroQol-5 Dimension(EQ-5D).Resource use and costs of healthcare, and days off work and normal activities, up to 90 days.

### Sample size and study duration

Good quality data for the incidence of VTE in low VTE risk surgical patients not receiving thromboprophylaxis is lacking. Data from the recently published GAPS RCT on moderate and high risk patients reported 29 (1.6%)/1858 VTE events at 90 days.^11^ The VTE rate for short-stay procedures in individuals formally assessed as being at low risk of VTE would be expected to be lower than this, however, as these short-stay patients are not receiving a thromboprophylactic dose of LMWH, we have conservatively assumed an overall control (no stockings nor drugs) VTE rate of 1.0%.

The sample size calculation is for a superiority comparison based on symptomatic VTE (DVT or PE) at 90 days at 90% power with a significance level of 5%, assuming 1.0% in the no stocking (control) and 0.5% in the stocking (active) groups.

Assuming an intraclass correlation coefficient (ICC) on the VTE at 90 days outcome of 0.001 (consistent with the control outcome rate varying uniformly between 0.5% and 1.5%)^18^ and a coefficient of variation of site size of 0.25 (consistent with sites varying according to a normal distribution mean=350 and SD=88, ie 95% of the sites would be between 174 and 526 participants), with 25 sites randomised to active and 25 sites to control, the study would need to recruit 17 500 patients. Allowing for 15% loss to follow, but no sites lost to follow-up, and adjusting for the group sequential design with one formal interim analysis at 50% with 90-day follow-up, 21 472 participants are required. We do not believe there will be any meaningful crossover. A check on the sample size assumptions will be incorporated when there are 10 sites across both arms that have recruited at least 100 patients each (checking on variability in the control outcome for ICC and checking zero crossover). At this stage, as well as confirming the overall maximum sample size, the schedule for a single efficacy or futility analysis at around 50% of the target recruitment with mature 90-day follow-up will be included.

### Interim analysis

When 50% mature primary outcome data are available, a formal interim analysis will be performed with the possibility of stopping early for futility (no prospect of a clinically meaningful treatment effect).

### Recruitment and randomisation

This is a cluster study, hence randomisation will be conducted at recruitment centre level rather than on an individual participant level. Each site will confirm capacity and capability with their local R&D team for participation in the trial prior to randomisation. Sites will be randomised by the Edinburgh Clinical Trials Unit by simple randomisation (1:1) via the Research Electronic Data Capture (REDCap) database, and will be adjusted for based on region, size and VTE compliance within the Trust. The trial manager will be informed of the treatment allocation via email, and the Trust will be informed via a treatment allocation letter. Sites and the study team will undertake local engagement to identify appropriate and willing specialties which form the basic centre unit. Recruiting centres will be randomised/allocated to either the intervention arm (where participants who undergo short-stay surgery will receive GCS to wear during their short-stay procedure) or the control arm (where no GCS will be provided to those undergoing short-stay surgery).

Due to the nature of this cluster design, patients are only required to consent to be contacted for follow-up (at 7- and 90-days post procedure).

Patients from a variety of surgical specialties will be included in this pragmatic trial. Adults who are scheduled to undergo short-stay surgery will be prescreened by a member of the direct care team and invited to speak to a member of the research team. Permission from the patient will be granted by the direct care team before any information is passed or approach made by the research team.

Recruitment will commence on 1 October 2022 for 30 months. The study will close on 31 December 2025.

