### Statistical analysis

All statistical analyses will be governed by a comprehensive statistical analysis plan, authored by the study statisticians and agreed by the independent Trial Steering Committee (TSC).

The main analysis will be according to the intention-to-treat principle and will compare the rates of VTE at 90 days, measured at an individual level, using hierarchical (multilevel) logistic regression, adjusting for any other prespecified strongly prognostic individual baseline covariates and site-level baseline covariates, with site itself as a random effect. This will be performed independently by the Edinburgh Clinical Trials Unit who will have sole access to the final REDCap dataset. The findings will be assessed for robustness against any missing data, first using multiple imputation assuming this data are missing at random and, if appropriate and the data permit, further sensitivity analyses will be attempted under any plausible missing data mechanisms not missing at random. Secondary outcomes will be analysed in a similar fashion with generalised linear models appropriate to the distribution of the outcome. Safety data will be summarised descriptively.

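### The protocol does not say that each site's participating specialties are fixed before its allocation is known, so case mix could come to depend on the arm

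*Protocol article*

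**What the plan says.** All the relevant steps are in one paragraph of the protocol article, under Recruitment and randomisation. In the order written:

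1. "Each site will confirm capacity and capability with their local R&D team for participation in the trial prior to randomisation".
2. Sites are randomised 1:1 by simple randomisation. The site factors named are region, size and compliance: the randomisation "will be adjusted for based on region, size and VTE compliance within the Trust".
3. The trial manager learns the allocation by email, and "the Trust will be informed via a treatment allocation letter".
4. "Sites and the study team will undertake local engagement to identify appropriate and willing specialties which form the basic centre unit".
5. "Recruiting centres will be randomised/allocated to either the intervention arm" or the control arm.

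The same section opens by saying that "randomisation will be conducted at recruitment centre level rather than on an individual participant level". It later says that "Adults who are scheduled to undergo short-stay surgery will be prescreened by a member of the direct care team". Under Statistical analysis, the main model is a multilevel logistic regression adjusted for prespecified individual and site-level covariates that are not named, "with site itself as a random effect".

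**The concern.** In a cluster trial the sites are randomised but the patients are not. The arms are comparable only if the arm does not influence who enters at each site. The choice of specialties is one place where it could.

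The article's own Introduction gives a reason why willingness might depend on the arm. It reports that current national guidelines recommend stockings for several kinds of surgery and only ask clinicians to consider them for others. A specialty in the first group has a reason to hesitate at a site told to give no stockings. It has none at a stocking site, because Interventions describes stockings as the current standard of care. The Introduction also says that thrombosis risk is higher for some procedures than for others, so specialty may be prognostic.

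If higher-risk specialties stayed out of no-stocking sites, the control rate would fall and a real benefit of stockings would look smaller than it is. That matters for the final result and for the interim analysis, which may stop the trial for futility. Analysis by intention to treat cannot correct this, because the patients who did not enter are not in the data. A site random effect models variation between sites. It does not remove a systematic difference between arms.

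**Working it through.** **Timing.** Of the five steps listed above, only step 1 carries a time, before randomisation. Step 4 has none. Its position after step 3 suggests selection once the arm is known. Step 5 mentions allocation again after the specialties have been identified, which suggests the reverse. No other section settles it. Blinding covers outcome assessment and follow-up data collection, not selection.

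**The plan's sample size, reproduced first.** Inputs from Sample size and study duration: 1.0% against 0.5%, 90% power, 5% significance (taken as two-sided), ICC 0.001, coefficient of variation of site size 0.25, mean site size 350, 25 sites per arm.

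- Individually randomised: 6256 per arm.
- Design effect: 1 + ((1 + 0.25²) × 350 − 1) × 0.001 = 1.371.
- Total: 2 × 6256 × 1.371 ≈ 17 152. This is within 3% of the stated 17 500, at which power is 90.6%.

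The plan's figure is not in dispute.

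**Illustrative size of a case-mix difference.** The article gives no event rates by specialty. I assume two groups of specialties with risks of 0.5% and 1.5%. These are the ends of the range that the article assumes for control rates between *sites*, and using them for specialties is my assumption. If the share of higher-risk specialties differs between arms by *s*, then

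shift in risk difference = *s* × (1.5% − 0.5%).

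| Difference in share | Shift (percentage points) | As share of the 0.5-point target |
|---|---|---|
| 5 points | 0.05 | 10% |
| 10 points | 0.10 | 20% |
| 20 points | 0.20 | 40% |

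**Effect on power when the shift hides a benefit.** The effective number per arm is 8750 / 1.371 ≈ 6383. A 10-point difference reduces the observed difference from 0.5 to 0.4 points. Power is Φ[(difference − 1.96 × SE₀) / SE₁], where SE₀ is the pooled and SE₁ the unpooled standard error.

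- Shift raises the stocking arm (1.0% against 0.6%): SE₀ = SE₁ = 0.158 points, so power = Φ[(0.400 − 0.309) / 0.158] ≈ 72%.
- Shift lowers the control arm (0.9% against 0.5%): SE₀ = SE₁ = 0.148 points, so power = Φ[(0.400 − 0.289) / 0.148] ≈ 77%.

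The second case matches the mechanism described under the concern. In the opposite direction, with no true effect and a 0.1-point shift in favour of stockings, the nominal 5% test rejects about 9% of the time.

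**The case against.** **The order of sentences is not a timeline.** This stands. A reader might infer that the protocol has specialties chosen after allocation. The document does not say so, and the sentence that follows fits selection beforehand. Tying one step to the time before randomisation also does not mean that nothing else happens then.

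**The unit is clear elsewhere.** This stands for the most part. Because specialties are said to form the basic centre unit, a reader might infer that the randomised and analysed units differ. But the Abstract, Study setting, Interventions, Sample size, Follow-up periods and Statistical analysis sections all treat the site or centre as the cluster. The natural reading is that the specialties together make up the centre. One sentence is loosely worded, and the analysis is not at the wrong level.

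**The plan already limits the damage.** This stands in part. The model allows prespecified prognostic covariates, and these could reduce an imbalance. Eligibility narrows the spread of risk: age 18–59, stay under 48 hours, a risk score of zero and no previous thrombosis. The strengths and limitations box says that balance of confounders must be shown. None of this can be assumed to remove the problem. A specialty that recruits in one arm only has no counterpart to be adjusted against.

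**The size is hypothetical.** This stands. The article gives neither specialty rates nor any evidence of imbalance. It would go too far to read the table as the bias expected in this trial.

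**Prescreening by staff who know the arm is inherent in an open cluster trial.** This stands, and the point does not rest on it.

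**Conclusion.** The point holds as a gap in what the protocol fixes. As written, it permits participating specialties to be chosen with the arm known, and nothing in the article rules this out. It does not establish that this will happen. Nor does it show a mismatch between the randomised and analysed units.

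If willingness did depend on the arm, the more likely direction, given the guidelines that the article describes, is that a benefit of stockings would be understated. On the illustrative assumption of 0.5% and 1.5% specialty risks, each 10-point difference in case mix costs 0.1 percentage point, a fifth of the target effect. A single such difference takes power from about 91% to between 72% and 77%. The multiplier depends wholly on the assumed gap between specialties: with half that gap, the shift is halved. The change is worth making because it is cheap before sites are randomised, whereas the selection cannot be undone afterwards.

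**What to change.** - **Lock the list.** Require each site to lodge its list of participating specialties with the trials unit before its allocation is released, and say so under Recruitment and randomisation. If sites already do this, one sentence settles the point.
- **Tie the analysis to the list.** Restrict the main analysis to patients from the listed specialties. A lock prevents later additions but cannot make a listed specialty recruit, so report by arm any that recruit nobody.
- **Define the unit.** State in the same section that the site is the randomised unit, matching the random effect in the main model, and that the specialties are the parts of the site that recruit.
- **Adjust for case mix.** Include specialty or procedure group among the prespecified covariates. The statistical analysis plan is the natural place, and its absence from the article is not itself a fault.

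The cost is a short form per site and less freedom to add specialties later, which could slow recruitment at some sites. The sample size is unchanged.
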